## Abstract

**Background:**

Nosocomial infections remain an important source of morbidity, mortality, and increased health care costs in hospitalized patients. This is particularly problematic in intensive care units (ICUs) because of increased patient vulnerability due to the underlying severity of illness and increased susceptibility from utilization of invasive therapeutic and monitoring devices. Lactoferrin (LF) and the products of its breakdown have multiple biological effects, which make its utilization of interest for the prevention of nosocomial infections in the critically ill.

**Methods/design:**

This is a phase II randomized, multicenter, double-blinded trial to determine the effect of LF on antibiotic-free days in mechanically ventilated, critically ill, adult patients in the ICU. Eligible, consenting patients will be randomized to receive either LF or placebo. The treating clinician will remain blinded to allocation during the study; blinding will be maintained by using opaque syringes and containers. The primary outcome will be antibiotic-free days, defined as the number of days alive and free of antibiotics 28 days after randomization. Secondary outcomes will include: antibiotic utilization, adjudicated diagnosis of nosocomial infection (longer than 72 h of admission to ICU), hospital and ICU length of stay, change in organ function after randomization, hospital and 90-day mortality, incidence of tracheal colonization, changes in gastrointestinal permeability, and immune function. Outcomes to inform the conduct of a larger definitive trial will also be evaluated, including feasibility as determined by recruitment rates and protocol adherence.

**Discussion:**

The results from this study are expected to provide insight into a potential novel therapeutic use for LF in critically ill adult patients. Further, analysis of study outcomes will inform a future, large-scale phase III randomized controlled trial powered on clinically important outcomes related to the use of LF.

**Trial registration:**

The trial was registered at www.ClinicalTrials.gov on 18 November 2013. Trial registration number: NCT01996579.

**Electronic supplementary material:**

The online version of this article (doi:10.1186/s13063-016-1590-z) contains supplementary material, which is available to authorized users.

## Background

Nosocomial infections (NIs) remain an important cause of morbidity, mortality, and increased health care costs in hospitalized patients [1–3]. This is particularly problematic in intensive care units (ICUs) where NIs occur in 25 to 35 % of ICU patients and account for approximately 25 % of all nosocomial infections in the hospital [4, 5]. In ICU patients, mechanical ventilation is an important risk factor for NIs as more than two thirds of infections originate at three major sites: the respiratory tract, the blood stream, and the urinary tract [6]. Further, since NIs are increasingly caused by multidrug-resistant bacteria, clinicians frequently prescribe broad spectrum antibiotic regimens. In turn, this sets the stage for pseudomembranous colitis (PMC), another potentially lethal NI [7]. The prevention of NIs has the potential to improve patient outcomes and reduce the cost burden of increasingly broad spectrum, prolonged courses of antibiotics administered for suspected or confirmed infections.

Lactoferrin (LF), an 80-kDa, multifunctional glycoprotein of the transferrin family, is distributed widely in humans particularly in secretions of exocrine glands and specific neutrophil granules. The highest concentrations of LF are found in breast milk and colostrum. As an important component of the human innate immune system, it has many appealing properties that may prove effective for the prevention of NIs [8]. LF has the ability to bind iron, an important element for microbial growth, thereby reducing its availability to microorganisms and making it bacteriostatic [9–11]. In addition, LF has bactericidal effects on microorganisms attributable to its highly cationic charged terminus, which binds to bacterial surfaces [12]. The binding of LF to the bacterial surface destabilizes the bacterial outer membrane, thus enhancing bacterial susceptibility to osmotic shock, lysozyme, or other antimicrobial molecules [13–15]. This antibacterial activity has been documented against many important human pathogens, including: *Escherichia coli*, *Staphylococcus aureus*, *Klebsiella* sp*., Acinetobacter* sp., *Pseudomonas* sp., *Salmonella* sp., and *Proteus* sp. [16–18]. Additionally, LF has been shown to exhibit activity against *Candida albicans* and *Candida krusei* and to inhibit the formation of biofilms by *Pseudomonas aeruginosa* and oral bacteria [19–21]. This may be an important attribute of LF as biofilm formation is a large contributor to device-related infections [22].

Other reported effects of LF include its ability to neutralize lipopolysaccharide (LPS) and promote the growth of beneficial bacteria in the GI tract including *Bifidobacteria* [23, 24]. Lastly, LF has the ability to modulate the immune system including increasing the size of Peyer’s patches, increasing serum immunoglobulin levels, decreasing inflammatory cytokines and increasing anti-inflammatory cytokines such as interleukin-10 (IL-10) [25]. In healthy human volunteers, the administration of bovine lactoferrin (bLF) was associated with increased T-cell activation (total, helper, and cytotoxic) and increased antioxidant status [26]. Although LF is a polypeptide, it is resistant to digestion in the digestive tract with 60 to 80 % of bovine LF exiting the stomach intact [27]. Biologically active peptides survive after transit through the small intestine with antibacterial activity remaining similar or increased compared to intact LF [28–30].

The properties of LF make it a potential tool for the prevention of NIs in critically ill patients since its enteral administration may reduce the overgrowth of pathogens, which is an important cause of NIs in the critically ill [31]. We hypothesize that the administration of LF per os and via the nasogastric route to critically ill mechanically ventilated patients will reduce NIs, reduce antibiotic usage, and result in improved patient outcomes and survival. To test our hypothesis, we will first conduct a phase II randomized control trial (RCT) of LF for prevention of NIs with antibiotic-free days as the primary outcome supported by biomarker and mechanistic data. The data from this study will inform whether to proceed to a larger definitive study. Herein we report the protocol for the phase II study which is written in accordance with standardized reporting guidance from SPIRIT (see Additional file 1).

## Methods/design

A phase II randomized, multicenter, double-blinded trial in five Canadian tertiary ICUs. Study sites include: Kingston General Hospital (Kingston, ON), Hôpital du Sacré-Coeur de Montréal (Montreal, QC), Sherbrooke (Sherbrooke, QC), Royal Columbian Hospital (New Westminster, BC), and Ottawa Hospital (Ottawa, ON). An overview of the study process is provided in Fig. 1.

**Fig. 1 Fig1:**
[figure not shown]
An overview of the study process

### Study population

Adult mechanically ventilated patients in the ICU meeting all of the inclusion criteria and none of the exclusion criteria.

#### Inclusion criteria

Adult patients (aged 18 years or older)Invasive mechanical ventilation for 48 h or lessPatient is expected to be mechanically ventilated for longer than 72 h

#### Exclusion criteria

Patient is expected to be in ICU for less than 72 h from the time of randomization (due to imminent death, withdrawal of life sustaining therapies, or discharge)Presence of a contraindication to enteral feedingLack of access to the oral cavityAn allergy or sensitivity to LF or bovine-derived proteins or milkPatient is immunocompromised (post organ transplantation, acquired immunodeficiency syndrome (AIDS), neutropenia (fewer than 1000/cc absolute neutrophils), corticosteroids (more than 20 mgs/day of prednisone or equivalent for more than 6 months))Fulminant liver failure or end stage liver disease (Child’s class C)Life expectancy less than 6 months due to preexisting conditionsPatient is pregnant or lactatingEnrollment in an industry-sponsored interventional trial (coenrollment in other interventional studies allowed if there is no interaction between the interventions)Patient has undergone prior randomization in this study

### Study intervention

Patients will be randomized to receive LF or placebo. Patients randomized to the LF arm will receive LF solutions delivered to the oral cavity as a mouth swab and LF down a nasogastric tube. The LF used for the study will be bLF, supplied by Advanced Orthomolecular Research [32]. The dosage of bLF will be a total of 2 g administered in four divided doses per day which is similar to that used in other human studies. Following enrollment, the study intervention will start within 6 h of randomization. Study treatment will be discontinued after 28 days from the time of randomization, permanent removal of the feeding tube, or death, whichever occurs first. All patients will receive standard ICU care for critically ill mechanically ventilated patients. The prescription of antibiotics will be left to the treating team.

### Random allocation

A password-protected web-based central randomization system is used to allocate patients to study treatments such that investigators, research staff and patients are blinded to the next allocation and an audit trial is maintained. Clinicians will remain blinded during the study, which will be maintained by administering LF or placebo in opaque syringes such that the placebo and active solutions are indistinguishable from each other. Randomization will be stratified by site using permuted blocks of variable size. The randomization list will be computer-generated by the trial biostatistician using SAS (SAS Inc., Cary, NC, USA) and securely stored by the study biostatistician and the IT manager of the central randomization system.

### Follow-up

Patients will be followed daily until day 28. Mortality will be determined for the ICU stay, hospital stay, and at 90 days. All patients will have blood samples drawn for biomarkers (C-reactive protein (CRP), procalcitonin (PCT), and IL-6), as well as for genome-wide expression profiling, at baseline and on days 3, 7, 14, 21, and 28. Cytokines will be measured using multiplex enzyme-linked immunosorbent assays (ELISAs), with samples prepared on site and shipped to a central laboratory for processing. Blood for gene expression analysis will be collected in PAXgene tubes, frozen according to the manufacturer’s protocol, and shipped to a central genomics facility for ribonucleic acid (RNA) extraction and expression profiling using the Affymetrix PrimeView microarray [33, 34]. Tracheal samples for bacterial cultures will be obtained at baseline and on days 3, 7, 14, 21, and 28. In addition, given the nature of the intervention, no specific provisions have been made for ancillary or post-trial care of participants.

### Adverse events

All patients will be monitored closely for the development of serious adverse events, and reported as per Good Clinical Practice [35], Health Canada [36] and local ethics’ requirements. For serious adverse events, a form on the electronic Case Report Form (eCRF) is completed by local research personnel to capture the pertinent data.

### Protocol violations

A protocol violation is defined as noncompliance with the study protocol and/or procedures. For protocol violations, local research personnel are required to complete a protocol violation report that is reported to the study leader.

### Data management

Enrolled patients are assigned a numeric identifier to maintain confidentiality and no personal identifiers are collected. All study data is entered into an eCRF (REDCap) [37], which is housed on a secure server at Queen’s University, Kingston, ON. Paper-based study material is stored in a secure location, with access limited to study personnel.

### Primary outcomes

The primary outcome for this phase II study will be antibiotic-free days, defined as being alive and free of antibiotics 28 days after randomization. This measure is similar to ventilator-free days, which is widely used in the critical care literature and incorporates antibiotic status, ICU status, and mortality in the 28 days from study enrollment [38].

### Secondary outcomes

*Feasibility (recruitment rates*, *protocol adherence*, *data completeness*, *and time required to capture data)*: the goal for the recruitment rate will be an average of 0.75 patients per week/per site. Protocol adherence will be considered successful if more than 80 % protocol adherence is achieved. Evaluation of protocol adherence will include administration of study medications, obtaining biological samples and carrying out laboratory testing protocols. The goal for data completeness is 100 %, but success will be defined at knowing the status of more than 95 % of the 28-day outcomes. Lastly, the time needed to capture required data will be used to determine the budget and feasibility of a future definitive RCT*Clinical outcomes*: antibiotic utilization will be measured by the prescription of new antibiotics after 72 h of admission to ICU, and number of defined daily doses (DDD) of antibiotics. Blinded central adjudication of nosocomial infection (longer than 72 h from admission to ICU) will be determined using standardized definitions and procedures. Change in organ function post randomization will be measured using the Sequential Organ Failure Assessment (SOFA) score [39]. We will also record hospital and ICU length of stay, and hospital survival and 90-day mortality*Laboratory and biochemical outcomes*: the effects of LF will be evaluated using biomarker analysis, i.e., measurement of levels of sequential PCT, CRP, and IL-6 at baseline, day 3, day 7 and then weekly until 28 days post randomization. Gastrointestinal permeability will be measured using the Lactulose/Mannitol Ratio at day 5 [40, 41]. Immune function will be evaluated based on the production of tumor necrosis factor alpha (TNF-α) in response to an LPS stimulation assay [42]. Rates of tracheal colonization will be determined by the number of tracheal samples positive for potential pathogens*Genomics substudy*: the biological mechanisms of LF action will be explored using gene expression profiling. In a subset of patients (continuously recruited from one study site), an additional tube of blood will be collected at the abovementioned time points for RNA extraction and gene expression profiling. Bioinformatic analyses will examine differences in gene expression at baseline between control and treatment groups, changes in the treatment group in response to therapy, and differences between patients with and without the primary outcome

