### Statistical analysis

#### Sample size

From a study that enrolled a similar population, the mean and standard deviation of antibiotic-free days was: mean (SD), 14 (9) [43]. A 25 % increase in antibiotic-free days would be clinically significant and feasible if LF has the expected biological activity. To detect a 25 % increase in antibiotic-free days to 17.5 days in the intervention arm with 80 % power at a two-sided alpha of 0.05, a sample size of 210 (105 subjects per arm) is required. We believe that this sample size will be adequate to reliably assess all feasibility and laboratory outcomes but may not be powered for all clinical outcomes.

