#### Analysis of primary and secondary outcomes

The main analysis will provide a histogram showing the distribution of the antibiotic-free days per arm. Although the antibiotic-free days will not be normally distributed, the sample is large enough that the mean will be approximately normally distributed, so the mean difference with corresponding 95 % confidence intervals and *p* values will be estimated by an analysis of variance blocking by site. A sensitivity analysis will use an exact permutation test stratified by site to confirm the main conclusion. For transparency we will report both the primary and sensitivity analysis.

Feasibility outcomes will not be compared by arm but will be provided overall using descriptive statistics (recruitment rates, adherence and completeness proportions and mean time needed to capture required data). Since there are multiple clinical outcomes that may have low power, we will avoid formal hypothesis testing and focus on presenting the between-arm difference in means or proportions with 95 % confidence intervals. All clinical analyses will control for site.

The distribution of the laboratory and biochemical outcomes will be depicted by arm over time using clustered boxplots. Statistical significance between arms at each time point will be tested by the Wilcoxon-rank sum test, but the multiplicity of tests and clinical important of differences will be considered when interpreting statistical significance. All analysis will adhere to the intent-to-treat principle. We expect the amount of missing data to be trivial (less than 5 %), but details of any missing data will be reported.

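### Tracheal colonization is announced as an incidence but measured by positive samples, which on either reading of the analysis plan does not give the number of patients newly colonized

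*Protocol article*

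**What the plan says.** In the Abstract (Methods/design) the protocol article lists among its secondary outcomes "incidence of tracheal colonization, changes in gastrointestinal permeability, and immune function".

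The Secondary outcomes section, under laboratory and biochemical outcomes, gives the measurement rule: "Rates of tracheal colonization will be determined by the number of tracheal samples positive for potential pathogens".

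The Follow-up section gives the schedule: "Tracheal samples for bacterial cultures will be obtained at baseline and on days 3, 7, 14, 21, and 28". That is six occasions, the first before treatment. The inclusion criteria allow up to 48 hours of ventilation before enrolment, so colonization may already be present at the first sample.

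For laboratory outcomes as a group, the section Analysis of primary and secondary outcomes plans "The distribution of the laboratory and biochemical outcomes will be depicted by arm over time using clustered boxplots", and adds: "Statistical significance between arms at each time point will be tested by the Wilcoxon-rank sum test". No separate rule is given for colonization.

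**The concern.** Incidence asks how many patients free of a pathogen at the start acquire one. The stated rule counts samples. It names no denominator, does not count each patient once and does not say how the baseline sample is treated.

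The Background says that enteral lactoferrin may reduce overgrowth of pathogens, and that biomarker and mechanistic data will support the primary outcome in deciding on a larger trial. Colonization is one of the outcomes closest to that mechanism. If it is reported as incidence but reflects existing colonization, repeat positives or time under sampling, readers may draw the wrong conclusion about acquisition. The direction could even mislead: the trial hypothesizes better survival, and patients who live longer can give more samples.

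**Working it through.** The article gives no numerical figure for colonization, so there is none to reproduce. The sample size of 210 concerns antibiotic-free days and plays no part here.

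**Step 1. Rule against target.** Take two patients with all six samples. Patient A carries the same organism at baseline and at every later visit: six positive samples, no new colonization. Patient B is negative until day 28 and positive then: one positive sample, one new colonization. The stated measure ranks A far above B; incidence counts only B.

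**Step 2. If samples are pooled over visits.** The inputs are assumptions, not figures from the document:
- Mean sampling time m, exponential: P(still sampled on day d) = exp(−d/m).
- Share b colonized at baseline, colonization persistent, acquisition hazard h per day the same in every scenario: P(colonized on day d) = b + (1 − b)(1 − exp(−h·d)).
- Expected positives per patient = sum over d = 0, 3, 7, 14, 21, 28 of the product of the two.

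With b = 0.30 and h = 0.05:

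| Day | P(colonized) | P(sampled), m = 7 | Product | P(sampled), m = 14 | Product |
|---|---|---|---|---|---|
| 0 | 0.300 | 1.000 | 0.300 | 1.000 | 0.300 |
| 3 | 0.398 | 0.651 | 0.259 | 0.807 | 0.321 |
| 7 | 0.507 | 0.368 | 0.186 | 0.607 | 0.307 |
| 14 | 0.652 | 0.135 | 0.088 | 0.368 | 0.240 |
| 21 | 0.755 | 0.050 | 0.038 | 0.223 | 0.168 |
| 28 | 0.827 | 0.018 | 0.015 | 0.135 | 0.112 |
| Sum | | 2.22 | 0.89 | 3.14 | 1.45 |

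The count rises by 63% (1.449/0.886 − 1) with no change in the acquisition hazard. Baseline samples make up 0.30/0.89 = 34% of positives at m = 7 and 0.30/1.45 = 21% at m = 14. Dividing by samples taken does not remove the dependence: 0.89/2.22 = 0.40 against 1.45/3.14 = 0.46.

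Over b from 0.10 to 0.50 and h from 0.02 to 0.05, the rise lies between 47% (b = 0.50, h = 0.02) and 91% (b = 0.10, h = 0.05). The baseline share lies between 10% and 42%.

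**Step 3. If each visit is tested separately.** Each patient then counts at most once per test and the baseline visit stands alone. But the quantity on day d is the share positive among those sampled that day. With the same b and h, day-14 positivity is 0.652, of which 0.30/0.652 = 46% was already present at baseline. On day 7 the share is 0.30/0.507 = 59%. Those sampled are also a shrinking group: 14% of patients on day 14 if m = 7, and 37% if m = 14. This is prevalence in a selected group.

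**Step 4. Clustering, only if samples are the units.** With an assumed 3 samples per patient and within-patient correlation ρ, the design effect is 1 + (3 − 1)ρ.
- ρ = 0.3: design effect 1.6, square root 1.265. An unadjusted interval is 1 − 1/1.265 = 21% too narrow.
- ρ = 0.6: design effect 2.2, square root 1.483. An unadjusted interval is 1 − 1/1.483 = 33% too narrow.

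**Step 5. What a patient-level outcome does and does not cure.** In the Step 2 model, the chance that a new acquisition is detected is the sum over d of P(last sample on day d) × (1 − b)(1 − exp(−h·d)). With b = 0.30 and h = 0.05 it is 0.13 at m = 7 and 0.23 at m = 14. Baseline and repeat positives are gone, but a crude proportion still depends on how long patients are observed. Death and end of sampling must therefore be reported with it.

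**The case against.** The strongest reply is that colonization belongs to the laboratory outcomes, for which the plan specifies a comparison at each time point. On that plan no patient is counted more than once in a test, baseline positives are not added to later ones, and within-patient correlation does not enter a single comparison. A rank-sum test on a yes/no result is valid, although boxplots show it poorly. This stands, and it limits the point.

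A reader might infer more than the document supports:
- **That baseline positives count as events and one patient counts six times.** The article does not say so; it only fails to exclude it. The word rates in the rule may imply a denominator, though none is given.
- **That a planned confidence interval is too narrow.** No pooled per-sample interval is planned for laboratory outcomes, so Step 4 is only a warning in case samples are pooled.
- **That the measure depends on ventilator time by design.** The Follow-up section sets fixed days and does not tie sampling to intubation. Death certainly ends sampling; that extubation does so is probable but inferred.

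It can also be said that clearance of existing colonization is a plausible effect of a bactericidal agent, that positivity over time would show it, and that randomization balances baseline positives in expectation. All three are fair. They are reasons to keep positivity by visit as a display, not to call it incidence. Finally, an article may leave detail to a fuller document. Here, however, the article states a measurement rule, and that rule does not match the outcome it names.

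**Conclusion.** The mismatch holds on either reading. Pooled, the measure is a sample count that does not exclude baseline or repeat positives and that grows with time under sampling. By visit, it is prevalence among those still sampled, selected by death and probably by extubation. Neither is the incidence announced in the Abstract.

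The size cannot be taken from the document. In the pooled illustration, doubling mean sampling time raises the count by 47% to 91% with acquisition unchanged. That rests on assumed exponential sampling time, persistent colonization and a constant hazard, and a doubling is a large contrast chosen to show the mechanism, not a forecast of the difference between arms. The document does not support a claim that the trial's result will be biased in a given direction.

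The change is worth making before analysis, but it concerns one secondary laboratory outcome of a phase II trial. The primary analysis and the sample size are unaffected.

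**What to change.** Define the outcome per patient: the first potential pathogen in a tracheal sample after baseline that was not in that patient's baseline sample, counted once. Compare arms as a difference in proportions with a 95% confidence interval, controlling for site, as the plan already does for clinical outcomes. Report death or end of sampling before acquisition as a competing event by arm, because the proportion alone still depends on time observed (Step 5).

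Keep positivity at each visit as a descriptive display, label it prevalence, and give the number sampled, so that any clearance effect remains visible. Use the same name for the outcome in the Abstract and the Secondary outcomes section. If samples are ever pooled as units, account for clustering by patient.

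The cost is wording in the analysis plan. The cultures are already scheduled, provided that organisms are recorded for each sample so that later findings can be compared with baseline. The drawback is fewer events than in the raw sample count, and so a less precise comparison.

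### The genomics substudy aims at lactoferrin's mechanism of action but lists no post-baseline comparison of lactoferrin with placebo

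*Protocol article*

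**What the plan says.** In the protocol article, under Secondary outcomes, the genomics substudy has a stated aim: "the biological mechanisms of LF action will be explored using gene expression profiling". Three analyses follow.

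1. The arms are compared before treatment, and
2. change is examined in the treated arm. Both stand in one phrase: "differences in gene expression at baseline between control and treatment groups, changes in the treatment group in response to therapy".
3. Patients are compared by outcome: "differences between patients with and without the primary outcome".

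On sampling, the same section says: "In a subset of patients (continuously recruited from one study site), an additional tube of blood will be collected at the abovementioned time points". The Follow-up section has blood drawn "as well as for genome-wide expression profiling, at baseline and on days 3, 7, 14, 21, and 28". Neither sentence restricts collection to one arm.

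Under Analysis of primary and secondary outcomes, a between-arm test over time is planned: "Statistical significance between arms at each time point will be tested by the Wilcoxon-rank sum test". That paragraph opens with its scope: "The distribution of the laboratory and biochemical outcomes will be depicted by arm over time using clustered boxplots". Secondary outcomes gives laboratory and biochemical outcomes and the genomics substudy separate headings.

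**The concern.** The aim is causal: what does LF do to gene expression? The comparison that randomization protects is LF against placebo after treatment has begun, and it is not in the list.

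The baseline comparison precedes treatment, so any difference there is chance and says nothing about LF. The treated-arm analysis is before-after without a control. These are ventilated, critically ill patients under standard ICU care, with antibiotics at the treating team's discretion, followed for up to 28 days. Their expression can change because they recover, deteriorate or receive antibiotics, and the group's average can change because patients die or leave. The article's wording credits that change to therapy in advance. The third comparison groups patients by outcome, not by arm. It also treats as present or absent something that the Abstract defines as a number of days and that the main analysis compares as a mean.

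The Background says that mechanistic data are to support the primary outcome and that the study will inform whether a larger trial follows. If the list is followed as it stands, the genomic part of that evidence could look positive for an inert product.

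**Working it through.** **Reading the listed analyses against the aim**

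| Listed analysis | After treatment starts? | LF against placebo? |
|---|---|---|
| Arms at baseline | No | Yes |
| Change in the treated arm | Yes | No |
| By primary outcome | Not stated | No |

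No row has both properties. The Wilcoxon tests would, but their paragraph covers the laboratory and biochemical outcomes, and nothing in the article extends them to gene expression.

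**Is there a figure to reproduce?** None is stated for the substudy. The main trial's figure reproduces: 2 × (1.960 + 0.842)² × 9² / 3.5² = 103.8, so 104 per arm against the stated 105. The point does not depend on it.

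**Illustration of size.** The documents give no subset size, shift or variance. All inputs here are assumptions:
- LF has no effect.
- One transcript shifts over time by δ = 0.5 SD of the within-patient change, equally in both arms.
- There are n = 10, 20 or 40 treated patients. For scale, 105 per arm spread evenly over five sites is 21 treated at one site, so 40 is a generous value.
- The two-sided alpha is 0.05, or 0.001 as a stand-in for a stricter genome-wide threshold.

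The treated-arm test is a paired t-test with n − 1 degrees of freedom and noncentrality δ√n. The probability of flagging is P(|T| > t critical) under that noncentral t distribution.

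| n treated | Noncentrality 0.5√n | Flagged at alpha 0.05 | Flagged at alpha 0.001 |
|---|---|---|---|
| 10 | 1.58 | 29% | 2% |
| 20 | 2.24 | 56% | 9% |
| 40 | 3.16 | 87% | 36% |

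With δ = 1, the noncentralities are 3.16, 4.47 and 6.32. The probabilities become 80%, 99% and 100% at alpha 0.05, and 16%, 71% and over 99% at alpha 0.001.

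The between-arm test compares mean change in LF with mean change in placebo. The shared shift cancels, so its noncentrality is δ − δ = 0 and it rejects at its nominal level.

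A simulation checked this: 4,000 runs per setting, baseline-to-follow-up correlation 0.5, which makes the SD of change √(1 + 1 − 2 × 0.5) = 1. For δ = 0.5 the treated-arm test was significant in 30%, 56% and 87% of runs. For δ = 1 it was 81%, 99% and 100%. The between-arm test stayed between 4.4% and 5.5% throughout.

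**Cost in precision.** With s the SD of change, the standard error within one arm is s/√n. Between two arms of n each it is s√(2/n). The ratio is √2 ≈ 1.41.

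**The case against.** The strongest reply is that this is one summary sentence in a condensed article. It does not say that these are the only analyses, and a fuller plan may contain the obvious contrast. The treated-arm phrase could also be read as change relative to control, and the article does compare arms at each time point for its other blood markers.

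Part of this stands. Model terms, the choice of days and the multiplicity method are details that an article may leave out. Their absence is no fault. But the article is not silent on the contrasts: it names them, and the named set does not fit the stated aim. The relative-to-control reading is possible, yet nothing in the sentence supplies a comparator.

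A reader might infer that the substudy cannot attribute any expression change to LF. The documents do not support that. Sampling is not restricted to one arm, so the data permit the randomized comparison. The fault is in the listed analyses.

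A reader might also take the baseline comparison as an error in itself. The article says only that differences will be examined. A descriptive look at comparability in a single-site subset is harmless, as long as it is not offered as evidence about mechanism.

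Finally, 87% should not be taken as the expected error rate. It is the high end of an assumed range for one transcript at a nominal 5% level. A smaller subset or a stricter threshold brings it down sharply, and a larger shift raises it.

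**Conclusion.** The point holds as a defect in the stated analyses. The substudy sets out to explore LF's mechanism, and no listed comparison contrasts LF with placebo after baseline. Change within the treated arm would carry the time course of critical illness under the label of a treatment response.

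How often that would mislead depends on inputs the documents do not give. Under no LF effect and a 0.5 SD shared shift, the range is 29% to 87% at alpha 0.05 and 2% to 36% at alpha 0.001, for 10 to 40 treated patients. The direction does not depend on these choices: with any shared shift, a treated-arm test responds to time as well as to treatment, and a between-arm test of change does not.

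The consequence is limited. The substudy is exploratory, no rule in the article makes gene expression a criterion for proceeding to the larger trial, and the primary, clinical and feasibility results are untouched.

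**What to change.** In the genomics paragraph, name the main contrast: the between-arm difference, LF minus placebo, in change from baseline, or in post-baseline expression adjusted for baseline, with false-discovery-rate control across transcripts. Keep the baseline comparison and the within-arm change as description only, and do not word the latter as a response to therapy. Relate expression to antibiotic-free days as a number of days, not as an outcome that a patient has or lacks.

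This changes wording only; the planned samples and arrays serve. The price is precision: with equal arms the standard error is about 1.41 times that of the within-arm contrast, so a small single-site subset will detect only larger effects.
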